## Abstract

**Background:**

Parental health literacy is an important determinant of children's health, especially during the critical window of early development in the first 3 years. As the information communication technology develops, health education *via* social media is widely used to deliver health information. However, few studies have explored the effect of intervention *via* social media on parental health literacy.

**Objective:**

This study aims to determine whether a WeChat official account-based health intervention can improve parental health literacy of primary caregivers of children aged 0 to 3 years in Minhang District, Shanghai, China.

**Methods:**

The cluster randomized controlled trial includes all 13 community health centers (CHCs) in Minhang District, Shanghai. We take each CHCs as a cluster in the randomization. The CHCs are randomly allocated to the intervention or the control group through random sequence generation. Ninety primary caregivers of children aged 0 to 2 years will be recruited from each CHC, 1170 in total. Caregivers in the intervention group will be provided with a series of video clips and online reading material links on scientific parenting *via* a WeChat account. Caregivers in the control group will receive printed educational materials with similar contents to the intervention group. All the participants will access routine child health care and be followed up for 9 months. Online assessment of health literacy will be conducted for both groups before and after the intervention. The primary outcome is the change in the total scores of parental health literacy using a validated instrument. The data of secondary outcomes, such as exclusive breastfeeding in the first 6 months, anthropometric measurements, and disease conditions, will be extracted from routine health care records. Generalized linear mixed model (GLMM) will be used for data analyses.

**Discussion:**

Compared with traditional health education, health intervention *via* WeChat official account could be a feasible and effective solution to improve parental health literacy.

**Trial registration:**

This trial is registered with the Chinese Clinical Trial Registry (ChiCTR): (#ChiCTR2000031711) on April 07, 2020.

## 1. Introduction

The “First Thousand Days” refers to the significant period from conception to the child's second birthday (1). During the first 3 years after birth, the quality of nurturing and care by caregivers plays an essential role in promoting children's immediate health and laying the foundation of their lifelong health (2). A growing body of evidence shows that parents' health literacy was closely associated with parenting practices. Children whose parents had low parental health literacy were more likely to experience poorer health outcomes, such as poor glycemic control (3), poor asthma control (4), and high emergency care utilization (5), especially for younger children. Low parental health literacy was also related to adverse health care behaviors, such as not practicing breastfeeding (6), incorrectly administering prescribed medicine (7), and allowing children exposed to more than 2 h television (8). However, limited interventions have been implemented to improve parental health literacy worldwide.

Health literacy, defined by the World Health Organization European Region (EU WHO) in 2013, is a multi-dimensional concept, defined as competencies of accessing, understanding, appraising, and applying health-related information within each of three health domains including health care, disease prevention, and health promotion (9). This conceptual model identifying twelve subdimensions can serve as a framework for developing measures and intervention strategies for enhancing health literacy. Based on this model, the Chinese Parental Health Literacy Questionnaire of Children 0 to 3 Years old (CPHLQ) was developed to assess parental health literacy (10, 11). By now, most studies just focused on single parenting knowledge or behavior and very few intervention studies have been carried out to improve overall parental health literacy among caregivers based on the integrated theoretical model.

With the rapid development of information communication technology, social media, such as Facebook, Twitter, and Instagram, has become significant channels and tools for information acquisition and exchange (12–16). WeChat, a free Chinese multi-purpose messaging and social media application, is the most widely and frequently used social media platform in China. It has monthly attracted more than 1.2 billion active users worldwide by the end of 2020 (17). WeChat official accounts (WOAs), a new function module of WeChat, can be used freely by governments, enterprises, and organizations to disseminate information and interact with their subscribers *via* text, image, audio, and video (18). In 2020, there were more than 360 million people acquiring information daily from WOAs (17).

WeChat has been increasingly used for disseminating health information. A recent national survey from 32 provinces and cities across China (19) found that one-third of participants regularly obtained health information through WeChat, and nearly two-thirds of participants reportedly expected to access health education from WOAs. The survey results also revealed that health education *via* WeChat and WOAs was convenient, timely, cost-effective, and protective of privacy. Substantial intervention programs *via* WeChat have proven to be effective and feasible in enhancing health literacy. For instance, a WOA-based intervention proved an effective and well-accepted strategy for improving malaria health literacy among Chinese expatriates in Niger (20). The results of a large-sample intervention in Sichuan, province of China, showed that WeChat platform helped to improve residents' health literacy and promote the development of healthy lifestyle (21). Health interventions *via* WeChat also have been shown with the potential to promote the satisfaction, accessibility, and convenience of child health care services (22), improve health management, and reduce medical cost (23).

Given the wide application of WOAs (24), we propose to conduct a cluster randomized controlled trial to determine the effectiveness of a WOA-based health intervention for improving the health literacy of primary caregivers with children aged 0 to 3 years in communities of Minhang District, Shanghai, China.

## 2. Objective

This study aims to develop an intervention program to improve parental health literacy among primary caregivers of children aged 0 to 3 years *via* WOA with clustered randomized controlled trial design in all 13 communities of Minhang District, Shanghai, China. The specific objectives of this cluster randomized controlled trial are:

(1) To develop a community-based health intervention program based on the integrated theoretical model of health literacy defined by EU WHO.(2) To implement the intervention among primary caregivers of children aged 0 to 3 years in the intervention group in communities of Minhang District, Shanghai, China.(3) To determine whether the WOA-based intervention is more effective in improving caregivers' health literacy, health-related behaviors, and health outcomes of the children compared with traditional health education.

## 3. Materials and methods

### 3.1. Overall study design

This cluster randomized controlled trial (cRCT) will be conducted in all 13 community health centers (CHC) of Minhang District in Shanghai. Each CHC will be designated as a cluster in the randomization. Prior to the participant recruitment, 13 CHCs will be randomized into the intervention group or the control group through random sequence generation. Eligible caregivers will be recruited after informed consent is obtained. Interventions will be implemented at the community level rather than the individual level to minimize contamination among participants within the same community. All participants will be followed up for 9 months (see Figure 1). We will compare the changes in scores of parental health literacy between the two groups before and after the intervention.

**Figure 1 F1:**
[figure not shown]
Research flow chart.

Ethical approval to conduct this trial has been granted by the Ethics Committee of Shanghai Minhang District Maternal and Child Health Hospital (#[2020]KS-01). The research is registered with the Chinese Clinical Trial Registry (#ChiCTR2000031711).

### 3.2. Study setting

The study will be conducted in Minhang district, Shanghai, China. Minhang district is located in the southwest of Shanghai, with 7,000 newborns annually and 12,760 children aged 0–3 years in 2020. A previous survey showed that the health professionals in Minhang district were facing huge gaps between limited health workforce and high demand for child care services (25). All 13 CHCs of Minhang district will be included in the study. Each CHC, where routine child health care services are provided for all children in the catchment area, will be a cluster.

### 3.3. Blinding

Due to the nature of the intervention, service providers and participants will not be blinded to the group allocation. Immediately after the baseline data collection, group allocation is revealed to participants. The statistician will be masked to group allocation during data analyses.

### 3.4. Participants and recruitment

Since the intervention will last 9 months and parental health literacy questionnaire applies to children only under 3 years, we will recruit primary caregivers of children aged 0 to 2 years at baseline. In this study, primary caregiver is defined as the person providing the major care for a child, including parents, grandparents, and other caregivers like nanny.

Recruitment will be conducted among caregiver-child dyads attending child health care in the child health clinics of CHCs. All study participants will complete a written informed consent before the randomization allocation is revealed. Once eligibility is established and consent obtained, caregivers will be invited to subscribe to the WeChat account for data collection or/and intervention delivery.

#### 3.4.1. Inclusion criteria

(1) Primary caregivers of children aged 0 to 2 years old.(2) Those who are above the third grade of primary school and able to communicate normally in oral and written form.(3) Voluntary participation.(4) Plan to live in the recruitment areas for at least a year.

#### 3.4.2. Exclusion criteria

(1) Not primary caregivers of children aged 0 to 2 years old.(2) Illiterate and unable to communicate in the form of speaking and writing.

### 3.5. Randomization and allocation concealment

All 13 CHCs in Minhang district will be randomly allocated to either the intervention or control groups through random sequence generation. In addition, group allocation will not be revealed to participants until they provide their written informed consent.

### 3.6. The WOA-based intervention program

#### 3.6.1. Intervention group

The WeChat account called Scientific Parenting is developed to conduct twice online evaluation and the 9-month intervention. Caregivers in both intervention and control groups will be asked to subscribe to and register with the account by entering information on their relationships with the child, the CHCs they belong to, and their children's birthday and unique health record number. Caregivers in the control CHCs cannot access the online intervention, which minimizes potential contamination caused by direct information sharing within the same CHC.

The intervention content was designed according to 12 sub-dimensions of health literacy defined by EU WHO (9). Based on the framework of health literacy, 15 key topics about children's health and development were generated and allocated to three health domains “health care, disease prevention, health promotion,” 10 in physical and 5 in psychological part through literature review and expert consultation. For example, there are physical and psychological health and development parts in health care domain. The physical health and development part includes three key topics of childhood common diseases “pneumonia and diarrhea,” antibiotic use, and routine health checkups (see Figure 2). The intervention contents of each key topic were developed to improve caregivers' capacity of accessing, understanding, appraising, and applying child health care information. Based on the key topics, the intervention materials include the following modules: essential information in child health care, neonatal nursing skills, neonatal health problems and management, scientific feeding guidance, childhood obesity prevention, child pneumonia identification, unintended injury prevention, hand-foot-mouth disease prevention, appropriate handwashing method, psychological problems and warning signs, early symptoms of autism, children physical activity guidance, children physical development and scientific feeding, guidance for parenting, and parent-child interaction games (see Supplementary Table S1).

**Figure 2 F2:**
[figure not shown]
A logic model for the WOA-based intervention.

Once subscribed to the account, caregivers in the intervention group will receive all the online health materials at once. They can self-navigate, select topics they are interested in, decide the order of material watching, and can access the intervention materials at their own pace. The online materials consist of two types of materials: video materials and online reading material links. The video materials include 4 video clips of experts' lecture each lasting 13 to 33 min and 6 animated video clips each lasting 1 to 5 min, with a total duration of 2 h. They could be watched repeatedly and the number of times of watching will be counted and recorded by the platform in each user's account. The caregivers in the intervention group can also access online reading materials related to scientific parenting through the provided links, such as e-books, websites, and other WeChat public accounts. Through this WOA-based intervention, participants in the intervention clusters can access reliable parental health information from a trusted official source. Supplementary Table S1 details the WOA-based health intervention program.

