Both baseline and final evaluation at the end of nine months survey will be conducted online *via* the aforementioned WOA. Besides collecting data for the outcome measures, we will collect demographic information of the caregiver-child dyads. We will also evaluate participants' engagement of the intervention through their completion rate of video clips and number of times of video watching, which both can be automatically tracked by a functional module designed by the research team on WOA platform.

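### As worded, section 3.6.1 lets the intervention materials open before the baseline CPHLQ is submitted, which does not fit section 3.3

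*Protocol article*

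**What the plan says.** All references are to the protocol article.

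- **Subscription.** Section 3.4 places it after eligibility and consent: "caregivers will be invited to subscribe to the WeChat account for data collection or/and intervention delivery".
- **One account, two uses.** Section 3.6.1: "The WeChat account called Scientific Parenting is developed to conduct twice online evaluation and the 9-month intervention". It covers both arms: "Caregivers in both intervention and control groups will be asked to subscribe to and register with the account". At registration the caregiver enters the CHC, which is the randomised unit.
- **Release of the intervention.** Section 3.6.1: "Once subscribed to the account, caregivers in the intervention group will receive all the online health materials at once".
- **Where baseline is measured.** Section 3.8: "Both baseline and final evaluation at the end of nine months survey will be conducted online", using that account.
- **When the arm is disclosed.** Section 3.3: "Immediately after the baseline data collection, group allocation is revealed to participants". Section 3.5: "group allocation will not be revealed to participants until they provide their written informed consent".
- **Intended order.** Abstract, Methods: "Online assessment of health literacy will be conducted for both groups before and after the intervention".
- **Other statements on delivery.** Section 3.6.2 gives controls a print pack covering similar ground once they are recruited. The limitations paragraph in section 4 also dates the online delivery from recruitment. Neither mentions baseline.
- **Use of the baseline score.** The primary outcome is the change in total CPHLQ score (section 3.8), and the baseline score is a covariate in the mixed model (section 3.10).

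**The concern.** A caregiver has to be in the account to answer the baseline questionnaire, and entry to the account is the stated trigger for the whole video and reading library. Taken literally, an intervention caregiver can look at the materials before or while answering. The materials cover topics that the CPHLQ scores, such as feeding, injury prevention and pneumonia. Six of the clips last only 1 to 5 minutes, so early viewing is practical.

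Two things are at stake. A baseline score raised by study material is no longer a pre-treatment measurement, yet it is subtracted in the primary outcome and adjusted for in the model. And receiving the library tells the caregiver the arm, which could affect whether and how the baseline is completed. The planned multiple imputation fills missing values; it does not repair a baseline that was recorded after exposure.

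**Working it through.** **Step 1: order of events.** The protocol gives no figure on this point to reproduce, so the check sets the sections side by side.

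| Event | Stated timing | Section |
|---|---|---|
| Consent | before allocation is revealed | 3.4, 3.5 |
| Subscription | after consent | 3.4 |
| Online materials released | on subscription; after recruitment | 3.6.1; 4 |
| Control print pack | after recruitment | 3.6.2 |
| Baseline CPHLQ | inside the account, so after subscription | 3.6.1, 3.8 |
| Arm revealed | straight after baseline | 3.3 |

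Release on subscription puts the materials at or before baseline. Since only the intervention arm receives the library, its arrival also reveals the arm. That cannot be squared with section 3.3 or with the abstract's order unless something holds the content back until the questionnaire is in. No section shown says so.

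**Step 2: is section 3.5 a further conflict?** No. It sets the earliest point at which the arm may be disclosed. Consent, then baseline, then disclosure satisfies both 3.3 and 3.5.

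**Step 3: how a lifted baseline reaches the estimate.** Let D be the true difference, d the mean baseline lift in the intervention arm minus that in the control arm, and b the slope of follow-up on baseline. Assume that early viewing leaves the 9-month score unchanged.

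- Change-score estimate = D − d
- Baseline-adjusted estimate = D − b × d

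Only the difference d matters. Equal lift in both arms (d = 0) leaves D intact.

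**Step 4: illustration.** D = 15 is the target difference in section 3.7. The values of b and d are assumptions; the documents give neither.

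| d | b | Change score | Baseline-adjusted |
|---|---|---|---|
| 0 | any | 15 | 15 |
| 2 | 0.6 | 15 − 2 = 13 | 15 − 0.6 × 2 = 13.8 |
| 5 | 0.6 | 15 − 5 = 10 | 15 − 0.6 × 5 = 12.0 |
| −2 | 0.6 | 15 + 2 = 17 | 15 + 0.6 × 2 = 16.2 |

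For b from 0.4 to 0.7 and d from 2 to 8, the adjusted estimate runs from 15 − 0.7 × 8 = 9.4 to 15 − 0.4 × 2 = 14.2. The last row of the table shows that the bias changes sign if controls are the more exposed arm.

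**Step 5: power, same caveat.** Section 3.7 plans 90% power for 15 points at 0.05, two-sided by section 3.10. On the normal approximation this fixes D/SE = 1.960 + 1.282 = 3.242, so no SD is needed. If a fraction f of the difference is lost, power = Φ(3.242 × (1 − f) − 1.960):

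- f = 0.10 (13.5 points): Φ(0.957) ≈ 83%
- f = 0.20 (12 points): Φ(0.633) ≈ 74%

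These figures show sensitivity. They do not forecast what will happen.

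**The case against.** The strongest reply is that the order is already fixed. Section 3.3 and the abstract put baseline first, and sections 3.1, 3.8.1 and 3.8.2 are written the same way. On this view the sentence in 3.6.1 describes the mode of delivery (everything together, at the user's own pace), and subscribing is merely a condition of access. The platform already restricts content by CHC, so an access control exists. Figure 1, the flow chart, is not shown and may give the order. An unlock setting is also the kind of operational detail that an article leaves to the full protocol.

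Much of this stands. Baseline first is clearly intended, and the platform may already hold content back. But the point does not rest on an omitted detail: the article states a trigger, and that trigger does not fit its own disclosure rule. Restricting by CHC separates the arms; it does not place baseline before release.

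Three stronger readings are tempting and are not supported:

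- **That section 3.5 sets a competing release point at consent.** It is a not-before condition, compatible with 3.3.
- **That only the intervention arm can be exposed early.** Controls cannot open the videos, but section 3.6.2 gives them similar content on paper, also without a baseline condition. A difference between arms is therefore possible but not established.
- **That the trial will lose some number of points.** Nothing says how many caregivers would view or read anything first. An average lift of 5 points before baseline would be a third of the 9-month target (5/15), which is a lot to assume.

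Providers are unblinded and CHCs are randomised before recruitment, so holding content back would not remove every route by which knowledge of the arm could act at enrolment.

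**Conclusion.** The point holds as a wording conflict with a possible effect on the primary comparison. As written, the release trigger in section 3.6.1 can precede baseline and disclose the arm, which sections 3.3 and the abstract exclude. Contamination is shown to be possible, not expected.

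Its net size is the between-arm difference in baseline lift, which the documents do not allow to be estimated. If that lift is larger in the intervention arm, both the change score and the baseline-adjusted effect are biased towards no difference. This route would then cost sensitivity and would not create a false positive. Differential completion of the baseline is a further possibility that cannot be quantified.

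Severity is moderate. The intended order is clear and the expected harm unknown, but a contaminated baseline cannot be recovered afterwards and prevention is nearly free. The conclusion rests on the visible text; Figure 1 or the full protocol could show that content is already held back, in which case only the wording needs correcting.

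**What to change.** 1. Reword section 3.6.1, section 3.6.2 and the delivery sentence in section 4 to match section 3.3, with one order: consent, subscription, baseline CPHLQ submitted, then arm revealed and materials released. Section 3.5 can stay as it is.
2. Set the platform to unlock content for a user only after that user's baseline questionnaire has been submitted.
3. Hand over the control print pack at the same trigger, so that both baselines are protected alike.
4. Record the time of baseline submission and of first viewing for each user, so that the order can be verified. The platform already counts viewings per account.

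The cost is a few sentences, a platform setting and a short delay in access for each participant. CHC staff would also need to confirm that the questionnaire is in before giving out the print pack. Sample size and analysis model are unaffected.

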#### 3.6.2. Control group

Caregivers in the control group will be provided with printed educational materials with similar contents as the video materials delivered to the intervention group, after recruitment. Caregivers of the control group can decide the orders of material reading according to their priority needs and interests. Supplementary Table S2 details the printed materials the control group will receive.

In addition, the same routine child health care services, including anthropometric measurements of weight and length, inquiry about feeding practice and dietary intake, and assessment of disease conditions will be provided to the intervention group and the control group (22).

